#### Exclusion Criteria:

- Previously documented atrial fibrillation or atrial flutter.
- Prior cardiac surgery (coronary artery bypass grafting, valve replacement or repair, pericardial stripping, etc) within the past 30 days.
- Hyperthyroidism.
- Have known skin allergies, conditions, or sensitivities (e.g. allergy to adhesives, psoriasis) as the Zio Patch should not be used on patients with known skin allergies, conditions, or sensitivities.
- Are receiving pacing therapy.
- Are anticipated to receive or require external cardiac defibrillation during the monitoring period.
- Are anticipated to have exposure to high frequency surgical equipment during the monitoring period.

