Physicians and/or medical centers that routinely investigate patients at high risk for atrial fibrillation will be selected for participation. The care team will identify eligible patients for this study at the time of their medical assessment. Additionally, patients may also be identified when they present as ‘walk ins’ to the cardiac investigations laboratory. All potential patients will be provided with an informed consent form. If a patient is then agreeable to inclusion in the study a coordinator will then take the patient to a private room, inform them of the study details, and provide them with adequate time to read the informed consent form (ICF). The study coordinator

will review the ICF with the patient and answer all of their questions. The patient will sign the ICF and the coordinator and the patient will proceed to the cardiac rhythm monitoring lab and/or the laboratory. Patients who presented with symptoms and a diagnosis of atrial fibrillation was confirmed at the time of the visit by an (ECG) will not be fitted with a monitoring device but provide blood for genetic testing and future research. Patients who otherwise meet inclusion/exclusion criteria will be fitted by the technician with a Zio® Patch or SpiderFlash-t™ loop recorder. All patients will provide a blood sample (in a 4 ml EDTA tube) for genotyping and a serum sample (in 2 x 10ml serum separating tubes) for future research. (These patients may also be fitted with a traditional Holter monitor).

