**Sorin SpiderFlash-t™ Loop Recorder**

Patients enrolled in British Columbia will be outfitted with a Sorin SpiderFlash-t™ Loop Recorder, an automatic and patient-activated long-term cardiac loop recorder. In addition to being patient activated, the Spider Flash is automatically programmed to activate recording if it senses atrial fibrillation. The recorder is water- and shock-resistant, and is supplied with a disposable water resistant plastic holster that hangs around the patient's neck. A patient diary with ECG connection instructions is provided to assist the patient with replacement of the recording electrodes to allow for bathing and skin care during the time the patient is wearing the recorder.

Events that are considered possible occurrences of atrial fibrillation will be adjudicated by a physician with expertise in cardiac rhythm interpretation. Primary end point events will be instances of atrial fibrillation/flutter.

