**AND**

- At high risk for atrial fibrillation, defined as any one of the following: ischemic stroke or TIA with no defined etiology (in prior 6 months) [3, 4, 6, 7], hypertension [33], increased body mass index ( $\text{BMI} > 30 \text{ kg/m}^2$ ) [33], heart failure [33], clinically significant murmur [33], prolonged PR interval on resting ECG [33], chronic kidney disease [34], hypertrophic cardiomyopathy [35], congenital heart disease [36], chronic obstructive pulmonary disease [37, 38], sleep apnea [39-41], thyroid disease [42, 43], family history of atrial fibrillation [44], diabetes [45] or excess alcohol consumption (Male  $> 14$  drinks/week, Female  $> 7$  drinks/week)[46].
- Age 40 years or older
- Capable of providing informed consent
- Capable of wearing a Zio Patch for up to 14 days or Sorin SpiderFlash-t™ loop recorder for up to 21 days.
- Capable of providing a blood sample

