## **9. Possible Risks and Analysis of Risk/Benefit Ratio**

In comparison with traditional outpatient cardiac rhythm monitoring, no new risks will be introduced by the study. It is anticipated that any complications with the Zio® Patch or Sorin SpiderFlash-t™ would be comparable to those already identified with commercially available devices used for traditional outpatient cardiac rhythm monitoring.

There is minimal risk to a patient receiving cardiac rhythm monitoring and, in general, complications for the Zio® Patch are related to the adhesive that affixes the patch to the subject. The Zio® Patch has been cleared for use by the FDA for patients who do not have known skin allergies or a family history of skin allergies. Company experience for skin allergies in 2011 is 0.02% in over 30,000 patients. Additional risks to the patient include the potential for emotional or mental discomfort of knowingly wearing a cardiac rhythm monitor for an extended period of time. We consider this risk to be quite low.

There is also minimal risk to a patient using the loop recorder and is confined to slight skin irritation where the electrodes are adhered to the skin.

In spite of all the safety measures that we will use, we cannot guarantee that the subject's identity will never become known. Although genetic information is unique to each subject, individuals do share some genetic information with their children, parents, siblings or other blood relatives. Consequently, it may be possible that genetic information from them could be used to help identify the study subject. Similarly, it may be possible that genetic information from the study subject could be used to help identify them. No personal data regarding analysis of the blood samples will be given back to the study subject.

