## **10. Risk Management Procedures**

### **Data Safety and Monitoring Board (DSMB)**

A DSMB will be assembled to provide an independent safety review of adverse events (AEs) and serious adverse events (SAEs) associated with the study. The DSMB will be comprised of individuals with expertise in cardiovascular disease, multi-center clinical trials and biostatistics:

[name]., M.S.: clinical trialist who has spearheaded multiple multi center clinical trials, currently the Director of Digital Medicine at the Scripps Translational Science Institute, previously at Geisinger Health in Pennsylvania.

[name].: clinical psychologist, Director of Social Sciences and Bioethics at the Scripps Translational Research Institute and clinical trialist.

[name]., M.P.H., F.A.C.P.M.: medical epidemiologist, biostatistician and Diplomat of the American Board of Preventative Medicine.

It is anticipated that the AEs associated with the study may include infection or irritation at the site of the phlebotomy, other complications from the blood draw, allergic reaction to the Zio patch adhesive and potential for loss of privacy and/or confidentiality.

The DSMB will review the safety data including all reported adverse events and SAE's after every 200 patients. At any time should safety concerns arise, the DSMB may convene an ad hoc meeting or make recommendations to the Sponsor about the appropriateness of continuing the study.

In addition to their routine safety review, the DSMB will assess the study's cumulative enrollment, and primary and secondary event rates in order to make appropriate recommendations on expected trial length, enrollment abnormalities or site-specific deviation from the protocol.

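### Section 9 describes the Zio Patch clearance as leaving out patients with a family history of skin allergy, but the Section 7 exclusion covers only the patient's own skin problems

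*Protocol*

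**What the plan says.** **Section 9 (Possible Risks and Analysis of Risk/Benefit Ratio).** The patch is described as "cleared for use by the FDA for patients who do not have known skin allergies or a family history of skin allergies". The same section says that patch complications generally come from the adhesive, and reports the company's 2011 experience of skin allergy as 0.02% in over 30,000 patients.

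**Section 7 (Exclusion Criteria).** The relevant exclusion begins "Have known skin allergies, conditions, or sensitivities (e.g. allergy to adhesives, psoriasis) as the Zio Patch should not be used on patients with known skin", and the sentence closes by naming the same three kinds of personal skin problem again. The device is the stated reason for the criterion.

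**Section 7 (Inclusion Criteria).** On ability to wear the device, the text asks only that the patient be "Capable of wearing a Zio Patch for up to 14 days or Sorin SpiderFlash-t™ loop recorder for up to 21 days". The one family-history item in the eligibility list is "family history of atrial fibrillation [44]", a qualifying risk factor that has nothing to do with skin.

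**Section 4 (Study Design).** "Patients who otherwise meet inclusion/exclusion criteria will be fitted by the technician with a Zio® Patch or SpiderFlash-t™ loop recorder". Two groups never receive the patch. Patients whose atrial fibrillation is confirmed by ECG at the visit "will not be fitted with a monitoring device but provide blood for genetic testing and future research". For the Canadian sites, "Patients enrolled in British Columbia will be outfitted with a Sorin SpiderFlash-t™ Loop Recorder".

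**Section 10 (DSMB).** Anticipated adverse events include "allergic reaction to the Zio patch adhesive".

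**The concern.** Both sections describe a limit on who should wear the same device, and they differ on one item. Section 7 is the text that a site applies when it enrols. Section 9 is the text that an ethics board reads when it weighs risk. A site that follows Section 7 to the letter has no prompt to ask about skin allergy in the family, so it can fit the patch to someone whom Section 9 places outside the described clearance.

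At stake is whether the device is used within the population that the protocol itself describes, and whether the risk section describes the patients actually enrolled. Section 9 also argues that the study adds no risk beyond ordinary outpatient monitoring. That assurance is harder to defend if the criteria allow use beyond the stated clearance.

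**Working it through.** No sample size, power or error rate enters this point, and the plan gives no figure to reproduce. The check is a comparison of text.

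**Step 1. Read the clearance statement.** A patient who does not have A or B has neither. Section 9 thus describes people with no known skin allergy and no family history of skin allergy.

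**Step 2. Set the two descriptions side by side.**

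| Patient characteristic | Section 9 clearance statement | Section 7 exclusion |
|---|---|---|
| Own known skin allergy | outside | excluded |
| Family history of skin allergy, none personally | outside | not mentioned, so eligible |
| Own skin condition, such as psoriasis | not mentioned | excluded |
| Own skin sensitivity | not mentioned | excluded |

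The sections agree on the first row. Section 7 is looser on the second and stricter on the third and fourth. The unprotected gap is the second row alone.

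**Step 3. Look for the missing item elsewhere.** The high-risk definition in Section 4 and the inclusion list in Section 7 do not mention family history of skin allergy. The fitting rules in Section 4 do not steer such a patient away from the patch.

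**Step 4. Follow one patient through.** Take a patient aged 40 or over with qualifying symptoms, one high-risk feature, a family history of skin allergy and healthy skin, who meets the other criteria.
- Section 7 inclusion: met.
- Section 7 exclusion: none applies.
- Atrial fibrillation on the visit ECG? If yes, no device is fitted and the gap does not matter.
- Enrolled in British Columbia? If yes, the loop recorder is used and the gap does not matter.
- Otherwise Section 4 allows the patch, for up to 14 days.

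**Step 5. Ask whether a later check would catch it.** The remote eligibility check in Section 18, on about 20% of enrolled subjects, asks for records of symptoms and of high-risk status. It does not ask for records on skin history.

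**Step 6. Scale of the hazard.** Taking the quoted 0.02% at face value, and supposing that every patient wore the patch, the expected number of skin allergies is 650 × 0.0002 = 0.13 at the enrolment figure in Section 13, and 1000 × 0.0002 = 0.20 at the figure in Section 6. Since some patients do not wear the patch, the expected number at that rate is lower. Whether the rate applies to patients with a family history is not stated.

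**The case against.** The strongest reply is that the two statements do not strictly contradict each other. Section 9 does not contain the word only. It describes a clearance within a risk narrative, while Section 7 sets eligibility, and a protocol may draw its exclusion differently from a device's clearance. The family-history clause may also be a loose account of the labelling, in which case no patient is affected and a few words in Section 9 need to go. Personal allergy and sensitivity, the more direct markers of risk, are already excluded, and adhesive reactions are among the events anticipated for DSMB review.

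Much of this stands. It rules out saying that both statements cannot be true, and it means that the labelling, which is not at hand, decides whether anyone is really outside the clearance. It does not remove the mismatch. Section 7 gives the device's limits as its own reason, so it claims to carry those limits into eligibility, and it leaves out one that Section 9 names without saying why.

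A reader might infer three stronger things that the protocol does not support:
- **That the 0.02% describes only the narrower population.** The figure is given as company experience. The link to the clearance statement is only that the sentences are adjacent, and nothing says how those patients were selected.
- **That a head count can be given.** The share of patients with a family history of skin allergy is not stated. Applying an assumed share to all 650 or 1000 patients would also count those in British Columbia and those diagnosed by ECG, who do not get the patch.
- **That adhesive allergy is the only device-related risk foreseen.** Section 9 also names distress from wearing a monitor and skin irritation from the loop recorder's electrodes.

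**Conclusion.** The point holds as an inconsistency between eligibility and the device description, confined to family history of skin allergy. A site can comply fully with Section 7 and still fit the patch to a patient outside the clearance as Section 9 words it. This can happen only to patients enrolled outside British Columbia who are not in atrial fibrillation on the visit ECG.

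Its size is modest. The number of patients concerned cannot be derived from the protocol, the hazard is a skin reaction reported at a low rate, and the power statement and event target are untouched. It still deserves correction, because it concerns who may wear the device and costs little to settle.

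The conclusion rests on reading Section 9 as a description of the whole cleared population, and on the text at hand. The appendices, including the patch instructions in Appendix 1, and the device labelling were not available. It would be wrong to conclude that the study uses the device off-label: that depends on the labelling, not on the protocol.

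**What to change.** Check the Section 7 exclusion and the Section 9 statement against the device's cleared labelling, and use the same wording in both. Either Section 7 comes to name family history of skin allergy, or Section 9 ceases to. Which is right is for the sponsor to settle from the labelling. Mirror the agreed wording in eligibility screening, so that sites ask the question that the protocol intends.

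The cost is a one-line amendment and, if family history is kept, one screening question. In that case a few otherwise eligible patients are lost. If it is dropped, enrolment does not change.

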#### 8. Possible Benefits

- Providing physicians data regarding the occurrence of arrhythmias for which patients may be asymptomatic and thus not observed by traditional 24-hour Holter monitoring, the knowledge of which may be of help in formulating treatment plans.
- Providing a potentially greater understanding of the characteristics (e.g. frequency, duration, rate, time of day) of arrhythmia episodes that are or are not associated with symptoms.

## **9. Possible Risks and Analysis of Risk/Benefit Ratio**

In comparison with traditional outpatient cardiac rhythm monitoring, no new risks will be introduced by the study. It is anticipated that any complications with the Zio® Patch or Sorin SpiderFlash-t™ would be comparable to those already identified with commercially available devices used for traditional outpatient cardiac rhythm monitoring.

There is minimal risk to a patient receiving cardiac rhythm monitoring and, in general, complications for the Zio® Patch are related to the adhesive that affixes the patch to the subject. The Zio® Patch has been cleared for use by the FDA for patients who do not have known skin allergies or a family history of skin allergies. Company experience for skin allergies in 2011 is 0.02% in over 30,000 patients. Additional risks to the patient include the potential for emotional or mental discomfort of knowingly wearing a cardiac rhythm monitor for an extended period of time. We consider this risk to be quite low.

There is also minimal risk to a patient using the loop recorder and is confined to slight skin irritation where the electrodes are adhered to the skin.

In spite of all the safety measures that we will use, we cannot guarantee that the subject's identity will never become known. Although genetic information is unique to each subject, individuals do share some genetic information with their children, parents, siblings or other blood relatives. Consequently, it may be possible that genetic information from them could be used to help identify the study subject. Similarly, it may be possible that genetic information from the study subject could be used to help identify them. No personal data regarding analysis of the blood samples will be given back to the study subject.

## **10. Risk Management Procedures**

### **Data Safety and Monitoring Board (DSMB)**

A DSMB will be assembled to provide an independent safety review of adverse events (AEs) and serious adverse events (SAEs) associated with the study. The DSMB will be comprised of individuals with expertise in cardiovascular disease, multi-center clinical trials and biostatistics:

[name]., M.S.: clinical trialist who has spearheaded multiple multi center clinical trials, currently the Director of Digital Medicine at the Scripps Translational Science Institute, previously at Geisinger Health in Pennsylvania.

[name].: clinical psychologist, Director of Social Sciences and Bioethics at the Scripps Translational Research Institute and clinical trialist.

[name]., M.P.H., F.A.C.P.M.: medical epidemiologist, biostatistician and Diplomat of the American Board of Preventative Medicine.

It is anticipated that the AEs associated with the study may include infection or irritation at the site of the phlebotomy, other complications from the blood draw, allergic reaction to the Zio patch adhesive and potential for loss of privacy and/or confidentiality.

The DSMB will review the safety data including all reported adverse events and SAE's after every 200 patients. At any time should safety concerns arise, the DSMB may convene an ad hoc meeting or make recommendations to the Sponsor about the appropriateness of continuing the study.

In addition to their routine safety review, the DSMB will assess the study's cumulative enrollment, and primary and secondary event rates in order to make appropriate recommendations on expected trial length, enrollment abnormalities or site-specific deviation from the protocol.

### **Loss of Privacy**

Only the investigator and research staff at the patient's site will have access to the patient's fully identified medical information. The information that matches the code to the identifying information will be kept in a safeguarded database that is password protected and any paper files will be kept in a secure location at the enrolling research site.

All blood samples will be labeled with a unique bar-code study subject number. This code will be used to identify these biological samples throughout their processing and storage in the research laboratory. There will be no traditional identifying information, such as name, birth

date, or social security number included with the biological samples. Only the site will have the information that matches the code to traditionally used identifying information.

Information from analysis of the coded samples and de-identified medical information will be placed in a controlled-access database on the internet. The database used for analysis will contain genotypes and clinical variables (listed in Appendices 4 and 5) and be coded so as not contain any traditionally used identifying information that could be used to identify the patient, and [name] will share these coded data sets with study non-Scripps co-investigators and their research staff.

A new Federal law, called the Genetic Information Nondiscrimination Act (GINA), generally makes it illegal for health insurance companies, group health plans, and most employers to discriminate against subjects based on their genetic information. This law generally will protect subjects in the following ways:

- Health insurance companies and group health plans may not request their genetic information that we get from this research.
- Health insurance companies and group health plans may not use their genetic information when making decisions regarding their eligibility or premiums.
- This new Federal law does not protect subjects against genetic discrimination by companies that sell life insurance, disability insurance, or long-term care insurance.

## **11. Recruitment**

Patients at high risk for atrial fibrillation will be identified during or prior to their appointment at the cardiac investigations laboratory.

## **12. Subject Payment/Costs**

Subjects will not be remunerated for participation in the study. There is no cost to the subject for study participation.

## **13. Estimated Duration of Study**

The study will be conducted at multiple participating research sites in order to meet the study enrollment goals in a timely manner. If the endpoint of 80 atrial fibrillation/flutter events have not been met at the end of 2 years, the timeline and enrollment may be extended until 80

endpoint (atrial fibrillation/flutter) events are recorded. If 80 endpoint events have occurred before 650 patients are enrolled, enrollment may be terminated before 650 patients are enrolled.

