## 2. Background

Atrial fibrillation is the most commonly encountered arrhythmia [1, 2] and when documented is predicted to be responsible for approximately 25% of strokes [3-5]. However, 25% of persons who suffer an ischemic stroke have no cause identified [3, 4, 6, 7]. In reality, many of these strokes are likely to be accounted for by atrial fibrillation [7, 8]. With 30 - 40% of ischemic strokes being classified as cryptogenic [9-14] it is imperative that greater efforts be taken to diagnose and treat those strokes that are due to treatable conditions such as atrial fibrillation. Because subclinical atrial fibrillation goes unrecognized by the patient it could be said to pose the greatest risk. Figures vary as to the prevalence of subclinical atrial fibrillation but implanted cardiac device studies in those without previously documented atrial fibrillation suggest it is indeed common [15, 16] and carries an increased risk of stroke or systemic embolism [3]. With recent studies highlighting the potential deficiencies of aspirin treatment in atrial fibrillation [17] it has become critical that we accurately identify all subgroups of atrial fibrillation and initiate appropriate treatment to reduce the risk of stroke.

Although atrial fibrillation can follow a familial pattern [18] more defined screening strategies need to be identified to target non-familial atrial fibrillation. To date, several genome-wide association studies (GWAS) have identified and replicated a panel of SNPs that occur more commonly in persons with atrial fibrillation. The SNPs with the most predictive utility are rs2200733 and rs10033464 on chromosome 4q25 [1, 19-27], rs2106261 on chromosome 16q22 [20, 21], and rs13376333 on chromosome 1q21 [22]. Several other SNPs have also had been associated with atrial fibrillation at a GWAS level ( $P < 5 \times 10^{-8}$ ) [47].

Of those SNPs on chromosome 4q25, rs2200733 was first reported to have an odds ratio of 1.84 for atrial fibrillation (1.51 - 2.23,  $P = 9.8 \times 10^{-10}$ ) and rs10033464 an odds ratio of 1.30 (1.00 -

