**Table 1.**

| rs#        | Locus | Gene    | OR source    | OR (95% CI)      | AF    |
|------------|-------|---------|--------------|------------------|-------|
| rs2200733  | 4q25  | PITX2   | [1] and [25] | 1.76 (1.49-2.07) | 0.115 |
| rs10033464 | 4q25  | PITX2   | [1] and [25] | 1.32 (1.23-1.42) | 0.097 |
| rs2106261  | 16q22 | ZFHX3   | [47]         | 1.24 (1.17-1.30) | 0.181 |
| rs13376333 | 1q21  | KCNN3   | [47]         | 1.18 (1.13-1.23) | 0.336 |
| rs3903239  | 1q24  | PRRX1   | [47]         | 1.14 (1.10-1.17) | 0.448 |
| rs3807989  | 7q31  | CAV1    | [47]         | 0.90 (0.87-0.92) | 0.42  |
| rs10821415 | 9q22  | C9orf3  | [47]         | 1.11 (1.08-1.15) | 0.397 |
| rs10824026 | 10q22 | SYNPO2L | [47]         | 0.87 (0.83-0.91) | 0.165 |
| rs1152591  | 14q23 | SYNE2   | [47]         | 1.13 (1.09-1.17) | 0.487 |
| rs7164883  | 15q24 | HCN4    | [47]         | 1.19 (1.14-1.24) | 0.168 |

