## 6. Statistical Considerations

SNP effect sizes and frequencies were determined from the literature and the International HapMap Project database as indicated in Table 1. Expected occurrences of atrial fibrillation in the two groups were calculated using reference to previous studies as outlined above [7, 8, 33]. We expect 80 atrial fibrillation events in a 1000 high-risk patients [48, 49]. Using these event rates and an alpha error of 5%, the power to detect an association between a 10-SNPs risk score and atrial fibrillation is >90%. The power to detect association between a 4-SNP risk score and atrial fibrillation is >80%.

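### The early-stop rule in Section 13 fixes the number of AF cases but not the number of AF-free patients, so a stop well below 650 would lose the power stated in Section 6

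*Protocol*

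**What the plan says.** Protocol Section 6 gives one planning scenario: "We expect 80 atrial fibrillation events in a 1000 high-risk patients". With "an alpha error of 5" per cent, it states that "the power to detect an association between a 10-SNPs risk score and atrial fibrillation is >90" per cent and that "The power to detect association between a 4-SNP risk score and atrial fibrillation is >80" per cent. The inputs are sourced as follows: "SNP effect sizes and frequencies were determined from the literature and the International HapMap Project database as indicated in Table 1".

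Section 13 governs when enrolment ends, and it works on the event count alone. If 80 events have not been reached after two years, enrolment may be extended until they are. In the other direction, "If 80 endpoint events have occurred before 650 patients are enrolled, enrollment may be terminated before 650 patients are enrolled". No lower limit on the total is given, no number of AF-free patients is required, and no power is stated for a total other than 1000.

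Two other sections bear on this. Section 10 has the DSMB look at cumulative enrolment and event rates, with safety reviews every 200 patients, but sets no numerical floor. Section 7 admits patients whose AF is first diagnosed by ECG on the day of enrolment. The protocol does not say whether they count towards the 80 events.

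**The concern.** The primary hypothesis in Section 3 compares a genetic score between patients with and without AF. The precision of that comparison depends on the size of both groups. A rule that counts only events suits a time-to-event design, where information follows the event count closely. Here it leaves the comparison group free to shrink.

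The problem arises when yield is higher than planned. All 80 events are in, the rule permits closing, and the comparison group is smaller than the one behind the stated power. A null result for the 10-SNP or 4-SNP score would then be read against a power that the trial did not have.

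**Working it through.** **Inputs from the protocol.** 80 cases in 1000 patients, so 920 AF-free (Section 6). Alpha 5% (Section 6). Odds ratios and allele frequencies for ten SNPs (Table 1); the first row, for example, reads "1.76 (1.49-2.07) | 0.115".

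**Assumptions, because the protocol does not state them.** A score weighted by log odds ratio; a two-sided test; independent SNPs in Hardy-Weinberg equilibrium; the 4-SNP score made of the first four rows of Table 1. Those four are the SNPs that Section 2 singles out ("The SNPs with the most predictive utility are rs2200733 and rs10033464 on chromosome 4q25", followed by rs2106261 and rs13376333).

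**Step 1: effect size.** The standardised difference in score between cases and non-cases is d = sqrt(sum of 2p(1-p)(ln OR)²).
- First SNP: 2 × 0.115 × 0.885 × (ln 1.76)² = 0.2036 × 0.5653² = 0.0651.
- First four SNPs: 0.0651 + 0.0135 + 0.0137 + 0.0122 = 0.1045, so d = 0.323.
- All ten SNPs: sum 0.1449, so d = 0.381.

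**Step 2: reproduce the stated power.** Information is I = 80 × (N − 80)/N, and power is Φ(d × sqrt(I) − 1.96). At N = 1000, I = 80 × 920/1000 = 73.6 and sqrt(I) = 8.579.
- 10-SNP: Φ(0.3806 × 8.579 − 1.96) = Φ(1.305) = 90.4%.
- 4-SNP: Φ(0.3233 × 8.579 − 1.96) = Φ(0.814) = 79.2%.

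Letting the score variance differ between cases and non-cases gives 91.1% and 80.6%. Simulation from a logistic model, with baseline AF risk of 8% and of 20%, gives 92-93% and 82-85%. The Section 6 figures are therefore reproduced, with little headroom. An unweighted allele count does not reproduce them (79.1% and 68.5%), which supports the weighted-score assumption.

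**Step 3: hold 80 cases and reduce the total.** Power is shown as 10-SNP / 4-SNP, two-sided 5%.

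| Total N | Yield 80/N | I | Closed form | Unequal variances | Logistic simulation (baseline 8% and 20%) |
|---|---|---|---|---|---|
| 1000 | 8.0% | 73.6 | 90.4 / 79.2 | 91.1 / 80.6 | 92-93 / 82-85 |
| 650 | 12.3% | 70.2 | 89.0 / 77.3 | 90.0 / 79.2 | 91-92 / 80-83 |
| 500 | 16.0% | 67.2 | 87.7 / 75.5 | 89.0 / 77.9 | 89-91 / 79-82 |
| 400 | 20.0% | 64.0 | 86.1 / 73.4 | 87.7 / 76.3 | 88-90 / 77-80 |
| 300 | 26.7% | 58.7 | 83.0 / 69.7 | 85.3 / 73.5 | 85-86 / 74-75 |
| 200 | 40.0% | 48.0 | 75.1 / 61.0 | 78.9 / 66.5 | 76-79 / 65-66 |

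A further simulation, which draws case genotypes directly from the allelic odds ratios, runs slightly higher: 90.4 / 81.2 at 400, 87.5 / 77.2 at 300 and 80.5 / 67.9 at 200. Every two-sided method misses both stated figures at 300.

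**Step 4: how many AF-free patients are needed?** To keep 90% for the 10-SNP score with 80 cases: 777 by the closed form, 572 with unequal variances, about 320 by the allelic simulation, and 227 by the closed form if the test is one-sided. A threshold exists inside the permitted stopping range under each of these methods, but its position depends heavily on choices that the protocol does not state.

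**The case against.** The case for leaving the rule alone has four parts.

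- **Near 650 the loss is negligible.** Information falls only from 73.6 to 70.2, because the 80 cases drive most of the precision. This stands. A reader might infer that any stop below 650 invalidates Section 6; the figures do not support that.
- **A very early stop needs an implausible yield.** The plan is 8%. A total of 500 needs 16%, 300 needs 27% and 200 needs 40%. A reader might infer that enrolment-day ECG cases make such yields likely. The protocol gives no expected number of these patients and does not settle whether they count as endpoint events, so it does not support that inference. Nor does it exclude the scenario: the 650 trigger itself already envisages a yield above 80/650 = 12.3%.
- **The rule is permissive and overseen.** Enrolment may be ended but need not be, and the DSMB would see a high yield. This is true, but neither provision tells anyone how many AF-free patients are enough.
- **Unstated assumptions matter as much as the rule.** With a one-sided 5% test, simulated power is still at least 90% and 81% at 300. The closed form puts the 4-SNP power at 79.2% even at 1000. The 4-SNP score is also not named among the Section 3 hypotheses, where the primary one concerns about ten SNPs. This stands, and it argues against writing any particular floor into the protocol from outside. A floor of 420 AF-free patients (500 in total), for example, would give about 89% and 79% at 20% baseline risk, just missing both targets.

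**Conclusion.** The gap is real and moderate. Section 13 permits a stop at which the Section 6 power no longer holds, and nothing else in the protocol prevents it. The loss is about 1 to 3 points just under 650. Both figures become marginal at about 400 to 500 patients. At 300 and below the shortfall is clear for both scores.

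These sizes assume the Table 1 effects, a weighted score, a two-sided test and the first four SNPs for the 4-SNP score. With a one-sided test the power would hold down to about 300 but not to 200, where it is 83.9% and 72.4% by the closed form and 86.8% and 77.1% with unequal variances. The documents support the statement that the rule does not protect the stated power. They do not support the statement that the trial is likely to lose it.

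**What to change.** Make one of two changes.

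1. In Section 13, allow early termination only when 80 events have occurred and a stated minimum number of AF-free patients, or a stated minimum total, is enrolled. The sponsor should derive that minimum from its own power method, with weighting, sidedness and the SNPs in the 4-SNP score made explicit.
2. Keep the rule, name the smallest total at which stopping is allowed, and restate the Section 6 power at that total.

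It would help to say at the same time whether AF found on the enrolment-day ECG counts towards the 80 events, since that determines how quickly the rule can be triggered.

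Either change takes about one sentence. The cost is losing the option of a very early stop under the first, or quoting a somewhat lower power under the second.
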